**Abstract**:

Metabolically Healthy Obese individuals (MHO) elderly are a minority phenotype and special, seemingly protected from the cardiometabolic disorders associated to excess adiposity. The aim of this study is to test whether the change of lifestyle by promoting physical exercise and recommendations of healthy Mediterranean-style diet (without caloric restriction) in elderly MHO is associated with changes in insulin sensitivity and whether modifies the metabolomic mechanisms, epigenetic patterns and gut microbiota in this population. For this purpose, 120 subjects will be recruited, with aged 65-80 years, with: a) a body mass index (BMI) ≥30-<35 kg/m2 mantained for at least 10 years before the recruitment, b) a HOMA-IR index <2.73, and c) ≤1 of the following 4 criteria: blood pressure ≥135/85 mmHg, fasting blood glucose ≥100 mg/dL, HDL-cholesterol <50 mg/dL in women and <40 mg/dL in men, triglycerides ≥150 mg/dL. The lipid profile, inflammatory biomarkers (hsPCR, IL6, TNFa, fibrinogen) and adipokines (adiponectin, leptin) will be analyzed. Epigenetic (methylation), metabolomic, and metagenomic (gut microbiota) studies, and of will be carried out and their possible relationship with different environmental pollutants will be analyzed.

**Background and current avalaible evidence**:

Obesity is a complex and heterogeneous syndrome that can be defined as a chronic disease mainly caused by the increament of fat tisue. The main cause of obesity is an imbalance in calories consumed and calories expended, although metabolic, physiology, genetic, celular, molecular, cultural and social factors may be involved (**1**). Globally, there is a trend toward consuming high-energy foods that are usually high in free sugars and fat, as well as a trend toward performing less physical activity. These trends are mainly caused by changes in social and environmental factors. A subset of these subjects is known as “metabollically healthy obese” (MHO) and, despite excess fat tissue, they are defined by a favorable metabolic profile. This profile is characterised by a high insulin sensitity, low visceral fat, low liver steatosis, normal blood pressure and favorable lipid, inflammatory, hormonal and inmune profiles. Although the mechanisms that could explain this benign metabolic profile of MHO subjects are still not well understood, the evidence suggests that certain factors such as the pattern of visceral fat deposition, birth weight, adipocyte size or expression of certain genes that regulate the differentiation and expansion of adipose tissue could be important (**2**).

There is currently great interest in investigating the MHO phenotype, as it can provide key data for a better understanding of the pathophysiological mechanisms of obesity. However, preventive interventions in this group remain controversial. On the one hand, it has been described that MHO individuals represent a subgroup of patients with better clinical evolution, since they will have a lower risk of developing cardiovascular disease or type 2 diabetes than the rest of obese subjects (**3-5**). They may not even get metabolic benefits from weight loss (**6,7**) or physical activity programs (**8**). Given its favorable cardiometabolic prognosis (**3**), a less intensive therapeutic approach could be justified (**9,10**). However, there are discrepancies regarding the clinical benignity of the MHO phenotype since it has been suggested that it can only constitute a simple transitional form to an obese phenotype with cardiometabolic alterations, although it is true that the phenotype MHO can be found in people of all ages (**11,12**).

Our research group has reported a high prevalence of obesity and metabolic syndrome among the adults in our population (Málaga, Andalusia) (**13,14**). However, the prevalence of MHO that we have documented is even lower than the reported by other authors. According to our data, only 9.6% of the obese population (2.2% of the adult population) would have a MHO phenotype (**15**). The MHO phenotype has been reported to be more prevalent in women and decreases with age (**3,4,16**). In our population, the MHO subjects had an average age almost ten years younger than obese patients with metabolic alterations (**15**), data confirmed by other authors (**17**). This might suggest that part of the MHO population could end up developing a cardiometabolic risk phenotype over time.

On the other hand, several epidemiological studies have observed that patients with overweight or moderate obesity have a lower risk of death and cardiovascular events than subjects with normal or low BMI (**18**), although this fact can be attributed to a form of reverse epidemiology. This phenomenon, called the "obesity paradox", is common in the elderly, in whom overweight or grade I obesity are associated with longer survival (**19**). BMI goal changes with age. In people older than 70 years, BMI goal is 30-32 kg / m2 (**20**), data in correlation with another study carried out in Spain with 1,008 people over 65 years of age followed for 11.6 years, where it was observed that the ideal BMI was in the range of 30-35 kg / m2. Median survival in grade I obese patients was 13.8 years, in overweight subjects 12.3 years, in normal weight subjects 10 years, and in lean subjects 5.6 years. In this age group, obese people survived an average of nearly four years longer than normal-weight subjects (**21**). Another reason that could explain the MHO phenotype in the elderly population is physical condition. It is known that 30% of the obese population is healthy due to their physical condition. The physical condition of the patient is rarely taken into account based on his aerobic or cardiorespiratory capacities. Because of this, MHO subjects have a 38% lower risk of death from any associated cause, compared to obese subjects with metabolic disturbances. On the other hand, the risk of developing or suffering from cardiovascular disease or cancer associated with their weight is reduced by between 30% -50% in this population (**22**, **23**).

Few studies have analyzed the MHO phenotype in the elderly, as well as the impact of lifestyle modification (diet, physical activity) on OMICS (epigenetics and metabolomics) and on the components of the intestinal microbiota of these patients. On the other hand, the exposure through the diet to perfluorinated pollutants, bisphenol A, parabens and benzophenones has not been enough studied in the population and it is very interesting to know their role as endocrine disruptors. Due to the possible implication of different genes and proteins involved in the molecular mechanisms that regulate the growth, expansion and homeostasis processes of adipose tissue, new studies are being generated to investigate the relationship between obesity and insulin resistance, without a known pathogenic concept established (**24**).

In conclusion, the study of elderly subjects with MHO phenotype can help to test the hypothesis of the transitional nature of this condition. Studies on the underlying mechanisms that lead the population to reach old age without developing insulin resistance and the pro-inflammatory changes that characterize obesity are of great pathophysiological interest and may help to identify possible therapeutic targets. With this background, we set out the objective of the -omic study of different candidate genes, as well as the involvement of the intestinal microbiota and the analysis of certain endocrine disruptors, and their relationship with lifestyle in elderly patients with a MHO phenotype. The identification of these elderly people who present differences in their profiles could help us to better understand why some obese subjects maintain a state of insulin sensitivity. In fact, research in these fields can elucidate new strategies for the prevention and therapy of the development of insulin resistance and atherogenesis in the obese population.

References:

1. Comuzzie AG et al. J Mol Med 2001;79(1):57-70

2. Primeau V et al. Int J Obes (Lond). 2011;35:971-81.

3. Calori G et al. Diabetes Care. 2011;34:210-5.

4. Pajunen P et al. BMC Public Health. 2011;1;11:754.

5. Khawaja KI et al. Singapore Med J. 2018 Feb 12. doi: 10.11622/smedj.2018019.

6. Karelis AD et al. Diabetologia. 2008;51:1752-4.

7. Dalzill C et al. Can J Cardiol. 2014;30(4):434-40

8. Janiszewski PM & Ross R.. Diabetes Care. 2010;33:1957-9.

9. Perseghin G. Diabetologia. 2008;51:1567-9.

10. Karelis AD. Lancet. 2008;372:1281-3.

**Study hypothesis**

H1. We postulate that the maintenance and/or weight loss produced by a change in lifestyle, mediated by changes in dietary habits and physical activity, and undertaken at the community level in the elderly Metabolically Healthy Obesity (MHO), will improve insulin sensitivity, compared to the non-responder group. Environment factors such as diet are able to modify the profile of epigenetic changes and, consequently, influence the development of obesityassociated diseases such as insulin resistance.

H2. We postulate that epigenetic modifications (on histones and in the promoter region) in genes involved in insulin resistance in obesity (epiobesigenes) are responsible for the development of the same, through the regulation of gene expression of genes regulating expansion ability, adipose tissue differentiation, adipogenesis, lipogenesis and inflammation.

H3. We postulate that the components of the microbiota have an immune function, a trophic function and digestive function. For this, interindividual variability exists depending on the composition of the flora, which can modify the energy value of food.

**Objectives:**

1. To analyze the demographic, anthropometric and lifestyle characteristics of the elderly MHO population.

2. To study the body composition and its relationship with the components of the diet in the elderly MHO population after a lifestyle intervention based on Mediterranean diet and physical activity recommendations.

3. To analyze the methylome and epigenetics involved in the pathways responsible for insulin resistance, inflammatory markers, lipid metabolism and adipokines. as well as the gene expression of methylases and how they affect the methylation profiles of an elderly MHO population.

4. To identify and study the alterations of methylome metabolites and the lipidomic pattern in an elderly MHO population undergoing a lifestyle modification intervention.

5. To explore the composition of the intestinal microbiota and its relationship with the components of the diet in the elderly MHO population.

6. To analyze the different endocrine disruptors and their relationship with lifestyle modification in the elderly MHO population.

**Study desing**

1. Open cross-sectional study that includes a MHOe population aged > 65 years of both sexes.
2. Inclusion criteria:
   1. Aged >65 years
   2. BMI ≥30-<40 kg/m2
   3. One or none of the following 4 cardio-metabolic disorders:
      1. Systolic blood pressure ≥140 mmHg and/or diastolic blood pressure ≥ 90 mmHg
      2. Triglycerides ≥150 mg/dL
      3. HDL-C <40mg/dL in men and <50mg/dL women
      4. Fasting blood glucose ≥100mg/dL, following the World Health Organisation criterion of MHO
3. Exclusion criteria:
   1. Diabetes
   2. Hypertension
   3. Previous cardiovascular disease (coronary, cerebrovascular or peripheral; aortic aneurysm, heart failure)
   4. Severe associated disease (advanced organ failure, dementia, cancer)
   5. Immobilized or terminally ill individuals
   6. Alcoholism or drug addiction
   7. Severe psychiatric illness
   8. Weight loss ≥5 kg in the last 6 months of unknown cause.
4. Recruitment and enrollment: recruitment will be carried out via visits performed to centers for the healthy elderly belonging to the Sports Area (Sport Medicine) of Malaga City Hall (Andalusia, Spain). Once the possible participants are selected, they are contacted and informed about the study design and objectives and summoned to the Department of Internal Medicine in the Regional University Hospital of Malaga. All participants in the study will give their written informed consent and protocols have been approved by the institutional ethics committee (Comité de Ética de la Investigación Provincial de Malaga (ref: PI18/00766-260718), belonging to the Andalusian Health Service).
5. Sample size: Simple Interactive Statistical Analysis (SISA) was used to calculate the sample size. We assumed a 95% confidence level (0.5% error), a statistical power of 80%, and a loss rate of 5%. The sample size needed is 150 patients.
6. Intervention: selected participants will follow a Mediterranean Diet advised by a nutritionist. The recommended caloric intake will be 1500-1750 kcal/day, distributed as follows: 30% of fats (5-8% of saturated fatty acids, 15-18% of monounsaturated fatty acids, 5-8% of polyunsaturated fatty acids and <300 mg of cholesterol/day), 55% of carbohydrates (< 10% of simple sugars, 40% complex sugars and low glycemic index) and 15% of proteins. The recommended Mediterranean Diet is based on the Trichopoulou criteria, prioritizing olive oil as the main cooking fat, consuming poultry or rabbit meat preferably rather than red meat and encouraging the consumption of fish, fruits, legumes and vegetables. Similarly, subjects will be encouraged to practice daily physical activity adapted to their age and physical condition, following the internationally-accepted physical activity guidelines (Physical Activity Guidelines for Americans. Chapter 5. Avalaible on: <https://health.gov/our-work/physical-activity/current-guidelines>). The intervention will last 24 months. Visits will be made at baseline and then at 4 and 12 months to reinforce the intervention and monitor the study variables and at 24 months to monitor for the last time the study variables.
7. Follow-up: medical visits will be performed at 4, 12 and 24 months after the start of the intervention. Anthropometric measurements will be taken, blood samples will be analyzed, and questionnaires will be completed in order to analyze the impact of the lifestyle intervention.
8. Outcomes:
   1. Primary outcome: composite outcome where the researchers will analyze the effectiveness of a multidisciplinary and multicomponent intervention carried out in the community setting, aimed at modifying the lifestyle (use of a Mediterranean diet and promotion of physical activity) to prevent the incidence of cardiometabolic alterations in elderly healthy metabolically obese subjects. This has been quantified as an improvement in Mediterranean diet adherence through food frequency questionnaires (baseline and 4, 12 and 24 months) and improvement in physical activity intensities, measured by accelerometry (minutes/day).

1. Nutritional assessment and monitoring: food intake analyzed using questionnaires at baseline and at 4, 12 and 24 months:

1.1. A non-consecutive, 3-day dietary record (two workdays and one weekend day), containing detailed information about food composition and cooking recipes over 72 hours

1.2. A food frequency questionnaire (number of times/day, number of days/week, number of days/14 days, number of days/month, rarely, or never)

1.3. Adherence to Mediterranean diet assessed by a validated 14-item food consumption frequency questionnaire

2. Physical activity monitored using a GENEActiv Actigraph GT3X+ accelerometer at baseline and at 4, 12 and 24 months. The accelerometer should be worn under the chest with a tight elastic belt to ensure close contact with the body. Recordings are made every day for at least 7 days (weekdays and the weekend) to take their hours of physical activity and sleep, except during water activities. Physical activity is also evaluated using the Rapid Assessment of Physical Activity (RAPA) questionnaire, a validated 7-item questionnaire at baseline and at 4, 12 and 24 months

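### The study is labelled cross-sectional but is a single-arm 24-month intervention, and its primary aim of preventive effectiveness cannot be answered without a comparator or an incidence measure

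*Protocol*

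**What the plan says.** - **Design label.** Study desing, item 1: "Open cross-sectional study that includes a MHOe population aged > 65 years of both sexes".
- **Who is treated, and for how long.** Item 6: "selected participants will follow a Mediterranean Diet advised by a nutritionist", with encouragement of daily physical activity, and "The intervention will last 24 months". No randomisation, control arm, allocation ratio or external comparator appears anywhere.
- **Follow-up.** Item 7: "medical visits will be performed at 4, 12 and 24 months after the start of the intervention", in addition to the baseline visit.
- **Primary outcome.** Item 8: "composite outcome where the researchers will analyze the effectiveness of a multidisciplinary and multicomponent intervention carried out in the community setting". The stated purpose of the programme is to keep new cardiometabolic disorders from arising, by way of diet and activity. The next sentence quantifies this as improved Mediterranean diet adherence (food frequency questionnaires) and improved activity intensity (accelerometry, minutes per day).
- **Comparator.** Study hypothesis, H1, expects insulin sensitivity to improve relative to non-responders. No other comparison group is named.
- **Selection.** Item 2 admits people with at most one of four cardiometabolic disorders. The Abstract adds HOMA-IR below 2.73, which is absent from item 2.

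**The concern.** Two statements in the Protocol do not fit the study it describes.

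The first is the label. A cross-sectional study has neither an intervention nor repeated measurement of the same people, and this one has both. The label tells an ethics committee, a registry and a reader of the results what kind of evidence to expect.

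The second is the aim. Prevention of incident disorders is a statement about what would have happened without the programme. If everyone is treated, that quantity is not observed. Change over two years in people over 65 cannot be separated from ageing, secular trend, selective dropout or the effect of being monitored. The measures chosen for the primary outcome also do not count incident disorders, so incidence would not be captured even descriptively within that outcome.

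At stake is what the study may conclude. A report that followed the Protocol's wording could present better adherence and activity as evidence that cardiometabolic disorders were prevented.

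**Working it through.** **Step 1. Label against described conduct (Study desing).**

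| Feature | Implied by item 1 | Described in items 6 to 8 |
|---|---|---|
| Intervention | none | diet and activity programme, 24 months |
| Measurements per person | one time point | baseline, 4, 12, 24 months |
| Groups | one | one, all treated |
| Type | cross-sectional | single-arm, longitudinal, before-after |

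The two columns cannot both be right. The sample-size paragraph (item 5) does not settle it. Its 150 cannot be reproduced, because no endpoint, effect size, variability or number of groups is given. It is consistent with about 142 evaluable people (142 / 0.95 = 149.5, rounded up to 150), but nothing in it indicates a control group.

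**Step 2. Aim against measure and comparator.** A claim about prevented incidence needs (a) a count of incident disorders and (b) a rate without the programme. The primary outcome supplies adherence and activity instead of (a), and the design supplies nothing for (b). H1's non-responders do not fill the gap. Response is observed after baseline, within the treated group, and is not randomised. People who respond may differ in health, motivation or function, and those differences may also drive insulin sensitivity.

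**Step 3. Regression to the mean in the variables used for selection.** This concerns HOMA-IR and the four criteria, not the primary measures. The source values below are assumptions, because the Protocol gives none.

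*HOMA-IR.* Assume a log-normal distribution with log-SD s = 0.55, single-measure reliability r = 0.6 to 0.8, no true change, and selection on one reading below 2.73. With a = (ln 2.73 − ln GM) / s and λ = φ(a) / Φ(a), the expected follow-up to baseline ratio is exp[(1 − r) · s · λ].

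| Assumed source geometric mean (GM) | a | λ | Ratio, r = 0.8 | Ratio, r = 0.6 |
|---|---|---|---|---|
| 1.5 | 1.089 | 0.256 | 1.03 | 1.06 |
| 2.0 | 0.566 | 0.476 | 1.05 | 1.11 |
| 2.5 | 0.160 | 0.699 | 1.08 | 1.17 |
| 4.0 | −0.695 | 1.286 | 1.15 | 1.33 |

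For example, GM 4.0 with r = 0.6 gives exp(0.4 × 0.55 × 1.286) = exp(0.283) = 1.33. The range is a rise of 3% to 33%.

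*Two or more of four criteria.* Simulate four stable traits (true-value correlation 0.2), each measured twice with independent error. Keep people with at most one criterion at the first reading and count those with at least two at the second.

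| Assumed source prevalence | r = 0.8 | r = 0.6 |
|---|---|---|
| 15% for each | 7% | 9% |
| 20% for each | 10% | 13% |
| 15% blood pressure, 25% for each other | 11% | 15% |
| 35% for each | 20% | 27% |
| 50% for each | 30% | 41% |

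The range is 7% to 41% with no true change in anyone.

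**The case against.** Single-arm studies are legitimate, and the primary measures are within-person changes that such a study can describe. That is right, and it is why the remedy is wording and not a control arm. It does not rescue the label or the prevention aim.

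Several stronger readings are tempting, and the Protocol does not support them:

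- *That the Protocol already claims effectiveness.* It says that effectiveness will be analysed. The fault is an aim that the design cannot meet, not an asserted result.
- *That regression to the mean biases the primary outcome or manufactures benefit.* Nobody is selected on diet adherence or activity, so selection does not touch those measures. In the eligibility variables the drift is towards apparent worsening, which works against a prevention claim.
- *That the artefact is large for certain.* The higher figures need high source prevalence. Recruitment is through municipal centres for healthy older people, and diabetes and hypertension are excluded, which makes lower values plausible. On the other side, the Background reports that only 9.6% of obese adults in the local population have the phenotype, which points to higher prevalence in an unselected source. The whole range has to be shown.
- *That a cross-sectional analysis will discard the within-person pairing.* No such analysis is proposed. Follow-up is planned in order to assess the impact of the intervention.
- *That the Background sentence "the study of elderly subjects with MHO phenotype can help to test the hypothesis of the transitional nature of this condition" is a study claim.* It is motivation and not one of the six objectives. Treated-only follow-up cannot show natural transition, but editing that sentence is optional.

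The choice of model, the baseline value and any sensitivity analysis can be left to a statistical analysis plan.

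**Conclusion.** The point holds in this form. The design label is wrong as written. The primary aim of preventive effectiveness cannot be met, because there is no untreated comparator and the outcome is quantified without any count of incident disorders. H1's contrast with non-responders is confounded and does not supply the missing comparison. These conclusions rest on the Protocol's text alone and on no assumed figure.

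The regression-to-the-mean figures are secondary. They rest on assumed source distributions, a log-SD of 0.55, a correlation of 0.2 and reliability of 0.6 to 0.8. They apply to the eligibility variables only, and the HOMA-IR figure applies only if the Abstract's threshold is actually used. Their width is a reason to treat changes in those variables as descriptive. It is not an estimate of what this study will see.

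**What to change.** 1. **Item 1:** relabel as an open, single-arm, longitudinal before-after intervention study of 24 months.
2. **Item 8, primary outcome:** restate as within-person change from baseline in Mediterranean diet adherence and in accelerometer-measured physical activity. Remove the aim of showing effectiveness in preventing incident cardiometabolic disorders.
3. **Study hypothesis, H1:** label the comparison of responders with non-responders as exploratory and associational.
4. **Add one sentence:** changes in the four criteria used for eligibility, and in HOMA-IR if the Abstract's threshold is applied, are descriptive and subject to regression to the mean.

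The cost is a few changes of wording and a weaker, descriptive conclusion. No control arm, added visit or added measurement is requested. Keeping the prevention aim would need a concurrent comparator and an incidence endpoint, which is a different study.

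### The sample-size statement misstates the error rate, conflicts with the Abstract's total, and gives too few inputs to reproduce 150 patients or 80% power

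*Protocol*

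**What the plan says.** The Protocol reports its calculation in item 5 of the Study desing section. It names the software ("Simple Interactive Statistical Analysis (SISA) was used to calculate the sample size"), lists the assumptions ("We assumed a 95% confidence level (0.5% error), a statistical power of 80%, and a loss rate of 5" per cent) and gives the result: "The sample size needed is 150 patients". It names no outcome, effect, SD or rate, test or sidedness.

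The Abstract gives a different total: "120 subjects will be recruited".

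The rest of the Protocol does not supply the missing inputs:

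- Item 8 describes a composite primary outcome, quantified by two separate measures: Mediterranean diet adherence by questionnaire, and physical activity by accelerometry in minutes per day. Both are measured at baseline and at 4, 12 and 24 months. Neither has a target change.
- H1, under Study hypothesis, concerns insulin sensitivity and compares with a non-responder group whose size is not given.
- Item 1 calls the study cross-sectional. Items 6 and 7 describe an intervention with repeated visits and no control arm.

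**The concern.** There are three defects in or around one short paragraph.

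First, the sentence that sets the error rate gives two values, 5% by implication and 0.5% in brackets.

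Second, the recruitment target is 120 in one place and 150 in another, so a reader of the results could not tell whether the study reached its planned size.

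Third, and most important, 80% power has meaning only for a stated effect on a stated outcome with a stated test. Item 5 gives none of these, and the Protocol offers at least three candidates: diet adherence, activity minutes, and insulin sensitivity against non-responders. If the result is null, nobody could say what size of effect the study was planned to detect.

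**Working it through.** **Inputs from the Protocol.** Item 5: 95% confidence, 0.5% error, 80% power, 5% loss, N = 150. Abstract: N = 120.

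**Assumptions made here, not in the Protocol.** Normal approximation, two-sided 5%, effects in SD units. The quantiles are z(0.975) = 1.960 and z(0.80) = 0.842, with sum 2.802.

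**1. Error rate.** 100% − 95% = 5%. An error of 0.5% would pair with 99.5% confidence. Reading 0.5% as a margin of precision does not help. For a proportion, n = 1.960² × p(1 − p) / 0.005², which is 38,415 at p = 0.5. At p = 0.022, the adult MHO prevalence quoted in the background, it is still 3,307.

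**2. The two totals.** Inflating 120 for 5% loss gives 120 / 0.95 = 126.3, so 127 (or 120 × 1.05 = 126), not 150. Going from 120 to 150 needs a loss of 1 − 120/150 = 20%, which is stated nowhere. The Abstract's 120 is a number recruited, so it cannot be read as the number completing.

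**3. Attempt to reproduce 150.** For a paired change of d SDs, n = (2.802 / d)², then divided by 0.95. The formula needs d, which item 5 does not give. For assumed values:

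| d (SD) | evaluable | enrolled |
|---|---|---|
| 0.2 | 197 | 208 |
| 0.3 | 88 | 93 |
| 0.4 | 50 | 53 |

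The total of 150 lies inside this range but follows from none of the stated inputs. It cannot be reproduced.

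**4. Working backwards from each total.**

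- 150 enrolled: 150 × 0.95 = 142.5, so 142 evaluable. Paired change detectable with 80% power: 2.802 / √142 = 0.235 SD.
- 120 enrolled: 120 × 0.95 = 114 evaluable. Paired change: 2.802 / √114 = 0.262 SD.
- 142 evaluable as two equal groups of 71: 2.802 × √(2/71) = 0.47 SD.

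The detectable effect therefore doubles depending on whether a within-person change or a two-group comparison was meant. Groups of unequal size, which responders and non-responders could well be, would detect only a larger difference.

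**5. What 120 instead of 150 would cost.** Take the effect that has 80% power with 142 evaluable (0.2351 SD). With 114 evaluable, power = Φ(0.2351 × √114 − 1.960) = Φ(0.55) = 71%.

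**The case against.** The strongest reply is that this is untidy drafting and not a flawed design. The conventional 95% is stated in words, and the bracket is almost certainly meant to be 5% or 0.05. The Abstract also differs from item 2 on age, BMI and blood-pressure criteria, which suggests two drafts that were never harmonised. The six objectives are descriptive or exploratory, and 150 patients would give 80% power for a modest paired change. Detail on the analysis may also sit in a statistical analysis plan that is not at hand.

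Much of this stands. The 0.5% alone is a minor correction. A reader who took it literally might infer that the test is to be run at 0.5% and that power is far below 80%: with 142 evaluable, Φ(0.2351 × √142 − 2.807) is about 50%. The Protocol does not support that reading, because it nowhere describes a test at 0.5%.

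The reply does not remove the other two defects. Unharmonised drafts explain how 120 and 150 came to coexist, but they do not say which applies. The missing inputs are also more than a detail left to a later document: the Protocol performs the calculation itself and reports its result, so what the result rests on belongs beside it.

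**Conclusion.** The point holds. The error rate is misstated, the two totals conflict and 5% loss does not reconcile them, and the 80% power can be neither verified nor attached to the primary outcome or to H1. The missing effect and outcome is the main defect, the 120/150 conflict comes next, and the 0.5% is the least of the three.

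A reader might go further and infer that 150 is too few, or that the study lacks 80% power. The documents do not show this. Whether 150 suffices depends on an effect that has not been stated, and 150 is adequate for a paired change of about 0.235 SD or more.

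The only loss that can be sized without using the 0.5% is the gap between the totals: about 71% instead of 80% power if 120 are enrolled, or a detectable paired change of 0.262 instead of 0.235 SD. These figures assume a two-sided 5% test of a single continuous variable and a paired analysis, which the Protocol does not fix.

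**What to change.** 1. In item 5, correct the error rate to 5% and say whether it is two-sided.
2. Give one total, the same in the Abstract and item 5, and state whether it is enrolled or evaluable.
3. For each primary component (diet adherence and accelerometry minutes per day), state the time point, the test, and the assumed effect and SD with their source, on which the 80% power rests. Say whether both components must improve or either suffices, since this changes the power. If the calculation was made for H1's comparison with non-responders, say so and give the assumed group sizes.
4. If no such assumption was made, drop the power claim and report the detectable difference for the chosen total, labelled as a consequence of that total. An effect worked back from 150 should not be presented as its justification.

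The cost is protocol wording. Once the inputs are stated, the power or detectable difference may prove less favourable than the present text suggests. Whether the total itself must change cannot be judged until then.
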